## Abstract

**Background:**

As food insecurity and healthcare costs are linked, healthcare entities (i.e., providers, healthcare systems, insurers) are increasingly interested in identifying and providing solutions to address food insecurity among their patients. Home-delivered meals are one long-standing solution to address food insecurity among homebound older adults. However, there is limited evidence about what mode of delivery is most effective in promoting community independence, reducing healthcare utilization, and improving quality of life as well as how these outcomes may vary as a function of people’s preferences for how meals are delivered to them.

**Methods:**

With extensive stakeholder input, we designed and implemented a pragmatic randomized comparative effectiveness study in which we will enroll 2300 older adults on waiting lists at home-delivered meals programs across the country and randomize them to receive for 6 months, either (1) weekday lunchtime meals delivered by a local volunteer or driver who also provides socialization and wellness checks or (2) biweekly delivery of 10 frozen meals to participants’ homes. Participant data will be combined with Centers for Medicare and Medicaid Services (CMS) data to calculate post-randomization institutional vs. community days. Baseline and 3-month surveys will evaluate secondary outcomes (e.g., food insecurity, loneliness, quality of life) and exploratory outcomes (e.g., nutritional risk). To examine heterogeneity of treatment effects, we will test for interactions between the two types of meal delivery and participants’ preferred mode of meal delivery as well as participants’ living arrangements.

**Discussion:**

This research will be the first to prospectively evaluate the comparative effectiveness of the two predominant meal delivery options. The knowledge generated from this research will be of value to healthcare providers, health systems, payers, community-based organizations, older adults, and their families, because it will identify the mode of meal delivery that best meets homebound older adults’ needs and promotes community independence. In addition, the experience of working closely with stakeholders in designing and conducting this trial will be useful to researchers seeking to engage with stakeholders in the development and evaluation of complex social service interventions while balancing regulatory, resource, and human subjects research considerations.

**Trial registration:**

ClinicalTrials.gov. NCT05357261. Registered on May 02, 2022

**Supplementary Information:**

The online version contains supplementary material available at 10.1186/s13063-024-08635-3.

## Introduction

Food insecurity among older adults is a critical public health issue with implications for families, the healthcare system, and society. Food insecurity disproportionately affects older adults who are racial or ethnic minorities, those with lower incomes, those who are disabled, and those living in non-metropolitan areas [1–3]. Food is a basic human need; among many food-insecure older adults, the “need for food competes with the need for other basic necessities such as medication, housing, utilities, and transportation” [4]. While food-insecure older adults can sometimes afford their food needs, they may not have the resources to access or prepare food because of lack of transportation, functional limitations, or health problems [1, 5].

Among older adults, food insecurity is associated with poor health status and health outcomes, and accounts for an estimated $130 billion annually in healthcare expenses[1, 6, 7]. Food insecure older adults are twice as likely to report fair or poor health, 50% more likely to have diabetes, three times more likely to suffer from depression, 30% more likely to have functional impairment, and nearly 60% more likely to have congestive heart failure or experience a heart attack [7]. Food insecurity can also pose challenges to chronic disease management and is associated with higher healthcare utilization and costs [8, 9]. Recognizing the link between food insecurity and health, health care entities (i.e., providers, healthcare systems, insurers) are increasingly interested in addressing food insecurity, among other social risk factors, through non-medical services such as home-delivered meals for older patients [10–15]. For example, in 2020, 42 states covered home-delivered meals in their Medicaid program [16]; and in 2022, almost 2 million Medicare beneficiaries were enrolled in a Medicare Advantage plan that offered a meals benefit [17].

There is limited evidence about which kind of home-delivered meals program is best for older adults. Home-delivered meals, long provided through a network of community-based organizations funded through the Older Americans Act, state dollars, and charitable contributions, grew out of a need to promote food security, socialization, and independence among older adults [18]. Until recently, meals have most commonly been delivered to older adults’ homes at lunchtime on weekdays using a volunteer or paid driver. Drivers often socialize and develop relationships with their clients, including providing an informal wellness check, sharing concerns about the client with the program, and often provide assistance beyond delivering meals (e.g., bringing in the mail, moving tripping hazards, troubleshooting air conditioning problems) [19]. It is believed that these social interactions contribute to the positive impact home-delivered meals have had on the health and healthcare utilization of a highly vulnerable population of homebound older adults experiencing food insecurity [20–25]. In recent years, vendors who provide mailed, frozen meals have gained popularity because they can provide a lower cost alternative: weeks’ worth of meals mailed to participants in one bulk package. While these meals have the same nutritional standards as daily-delivered meals (1⁄3 of older adults’ Dietary Reference Intake) [26], there is limited evidence on how satisfaction with, and the health benefits of, the frozen, mailed meals may differ from the traditional daily-delivered meals provided by community-based organizations. Prior research suggests that older adults who receive daily-delivered meals may have lower rates of loneliness and falls than those who receive frozen, once-weekly delivered meals from these community-based organizations [24, 25]; however, overall differences in health and healthcare utilization attributable to the two meal delivery methods remain unknown.

An important aspect of addressing food insecurity among homebound older adults is doing so in a way that aligns with their preferences. However, there is limited evidence about which mode of home-delivered meals older adults prefer. Many healthcare entities and community-based organizations strive for person-centered care, but there is little evidence to guide them on what mode of meal delivery older adults prefer or how receiving meals that older adults prefer may affect satisfaction and ultimately outcomes. Therefore, decision-makers have little evidence on either (a) which mode of delivery is more effective in reducing costly healthcare utilization and improving older adults’ quality of life and (b) how the effect of meal delivery on health and utilization outcomes may vary as a function of older adults’ meal delivery preferences.

To address these gaps in knowledge, we are conducting a multi-site, randomized pragmatic comparative effectiveness study with two parallel arms (the two modes of meal delivery) and a primary endpoint of institutional healthcare use in the 6 months after enrollment. The objective of this paper is to describe our protocol for the trial and present how it was shaped by stakeholder input (e.g., older adults receiving meals, meal providers, healthcare representatives). We specifically highlight the regulatory and resource challenges in responding to stakeholder input when designing and implementing this study.

## Methods

### Overview

The Deliver-EE: Evaluating Effects of Meal Delivery on the Ability of Homebound Older Adults to Remain in the Community Via A Pragmatic, Two-Arm, Randomized Comparative Effectiveness Trial, also known as The Deliver-EE Trial, was developed and is executed in partnership with Meals on Wheels America (MOWA), MOWA’s participating member programs, and a diverse group of stakeholders. In the conceptualization phase of the project, we worked with stakeholders to determine the most feasible study design and to anticipate system and local contextual barriers to study implementation, such as variation in meal prices by region. As a result of this engagement in the planning phase, we revised the analytic plan and site selection criteria and made changes to the protocol before submitting our application for funding consideration.

After funding was received (11/2021), we recruited 26 individuals to serve on two advisory panels: the Lived Experience Panel and the Systems’ Perspective Panel. Individuals serving on the Lived Experience Panel represent the frontlines of meal delivery and have unique knowledge about the interpersonal interactions and lived experiences of receiving and delivering meals. These members include older adults receiving meals from participating programs, care partners of older adults receiving meals, and volunteer and paid meal delivery drivers. The second panel represents the “Systems’ Perspective.” Members include representatives from the financial, clinical, regulatory, and operational environments in which meal delivery to food insecure older adults operates. These individuals include representation from healthcare plans, integrated care organizations, geriatric home care clinician researchers (including a practicing geriatrician with a home care practice and an advanced nurse practitioner who makes house calls), a registered dietitian, an expert in the integration of social services and medicine, and three home-delivered meals volunteer drivers from programs not participating in the trial. The panels began meeting with the research team in February 2022.

Brown University ceded regulatory oversight of the study to Advarra, Inc., an independent Institutional Review Board (IRB). This study was approved by the Advarra IRB as a minimal risk study. We do not have a Data and Safety Monitoring Board; any protocol deviations are reported to the Advarra IRB. Monthly enrollment reports are created by the research team and shared with the trial funder. Protocol amendments are shared with the funder and updated in the contract and clinical trial registry. In writing this report, we utilized the SPIRIT checklist to ensure the completeness of our trial protocol [27].

### Setting

The Deliver-EE Trial began enrollment in May 2022 and is expected to reach its enrollment target by December 2024. We are targeting enrollment of 2300 homebound older adults ages 66 years and older (to allow for a 1-year look back of their Medicare data) on waiting lists at ten Meals on Wheels programs across the country (a list of sites and their location is included in the Acknowledgements). Sites vary by geographic location, size, and demographic characteristics. We selected our study sites based on the size of their waiting lists and their capacity to serve participants. All participating programs agreed to provide administrative support, including sharing their waitlist and meal-delivery information, as well as provide meals using their standard processes to participants enrolled in the daily-delivered meals arm.

### Inclusion and exclusion criteria

To participate in the study, individuals must be 66 years of age or older, be on a waiting list at a participating program, and reside in a program’s daily service area (all areas served by programs may not have daily deliveries because of logistical and resource limitations). Individuals whose primary language is not English or Spanish, who have end stage renal disease requiring specialized diets, and those who are unable to participate in a phone survey/interview (e.g., difficulty hearing and speaking, lack of comprehension of study purpose, do not have a working phone) are ineligible for participation.

### Modes of meal delivery

The two treatment arms of the intervention are the two predominant modes of meals delivery: drop-shipped frozen meals and daily-delivered meals. All participants randomized to the daily-delivered meals arm receive lunch-time meals that meet national Title III requirements (i.e., (1⁄3 of older adults’ Dietary Reference Intake) [26]) delivered to their homes, five times per week, by a Meals on Wheels program employee/volunteer who socializes with the participant and provides an informal wellness check—all of which represent usual practices of Meals on Wheels programs nationwide and are tailored to the needs of participants and each program’s available resources. All participants randomized to the drop-shipped meals arm receive 10 frozen meals that are mailed to their home every 2 weeks from a vendor who provides meals meeting the same nutritional guidelines as the participating Meals on Wheels programs for 6 months. Participants may opt to stop receiving meals at any time and programs may discontinue meal service for noncompliance. Participants who discontinue meals will remain enrolled in the study and their data will be tracked. At the completion of the 6-month study period, participants continue to receive meals from participating programs pending meeting eligibility criteria and availability of resources.

### Recruitment and randomization

We developed the recruitment plan in partnership with participating programs and our advisory panels. To identify potential participants, Meals on Wheels program staff share demographic and contact information about individuals on their waiting lists who meet inclusion criteria with the research team. The research team sends an introductory packet about the study by mail and then contacts these individuals by telephone to screen, obtain informed consent, conduct the baseline survey, and randomize them to the two treatment arms (see Fig. 1).

**Fig. 1 Fig1:**
[figure not shown]
Deliver-EE SPIRIT study schedule

Participants are assigned by the research team to receive either daily-delivered meals or drop-shipped meals with a 1:1 allocation using stratified randomization. Randomization stratification variables include the program, the personal meal preference (daily/no preference vs. frozen), and the living arrangement (alone vs. with others). Randomization occurs at the end of the baseline survey.

### Masking

Participants are unable to be blinded to their randomized condition. The research staff conducting the follow-up surveys and the biostatistician conducting the outcomes analyses are blinded to the randomized condition.

### Consent

The informed consent process begins with the potential participant receiving an informational packet containing details about the study. The packet contains four items: (1) a welcome letter that provides an overview of the research opportunity, (2) a Letter of Support from the participating program, (3) a “Frequently Asked Questions” document addressing potential questions in user-friendly language, and (4) an Informed Consent Document.

Approximately 2 weeks after the packet is mailed to the potential participant, a trained interviewer from the Brown University Survey Research Center calls the potential participant at their preferred telephone number provided by the program. If the potential participant is not reached in the first attempt, the interviewer makes a minimum of two additional telephone calls and one text message, if applicable, at different hours and days over approximately 2 weeks. When a potential participant is successfully contacted, the interviewer reviews the most salient points from the informed consent document using an IRB-approved script, answers any questions about the study, collects a verbal consent to participate, and immediately begins the baseline survey.

### Data collection

Survey data are being collected for all participants pre-intervention (baseline) and 3 months later (follow-up). Survey questions include items to assess demographics, preference for daily or drop-shipped meals, and health and well-being (e.g., food insecurity, health-related quality of life). To assess our exploratory outcome, nutritional risk (described below), we are conducting a longer survey that includes the Dietary Screening Tool with 600 randomly-selected participants. Additionally, we are conducting semi-structured telephone interviews with approximately 50 participants two months after they begin receiving services to collect information about their experiences receiving meals, how these services may have impacted their lives, and their satisfaction with these services. We are purposefully selecting participants for the semi-structured interviews across programs, treatment arm, preference, and living situation. A member of the research team contacts a participant selected for a qualitative interview and invites them to participate. These interviews take approximately 30–45 min to complete. Additional data sources include participant and service data from participating Meals on Wheels programs and claims, assessment, and enrollment files from the Centers for Medicare and Medicaid Services (CMS). We obtained a HIPAA waiver of authorization to use the CMS data. See appendix for information on data management and maintaining confidentiality.

### Outcomes and measures

When writing the research proposal for the funding that supports this work, we established the relevance of the proposed study with a broad group of stakeholders, concentrating our efforts on intended end users of the results: healthcare entities, meal providers, homebound older adults, their care partners, and the drivers who deliver meals. These stakeholder partners identified the person-centered outcomes (see Table 1) to include in the study.

**Table 1 Tab1:** Deliver-EE clinical trial outcomes

Primary/secondary/exploratory	Name of outcome	Specific measure to be used	Timepoints	Data
Primary	6-month ratio of days in institutional settings	Ratio between the number of days that are spent in an institutional setting (i.e., acute care hospital, psychiatric hospital, long-term care hospital, nursing home, or skilled nursing facility) and the number of days alive in the 6 months following receipt of meals	6-month	Medicare claims
Secondary	3-month ratio of days in institutional settings	Defined similarly to the primary outcome, but assesses the immediate (3-month) impact of meals on days spent in institutional settings	3-month	Medicare claims
Secondary	Food insecurity	The 6-item Household Food Security Scale Short Form [27]	3-month	Survey
Secondary	Subjective isolation/loneliness	UCLA 3-Item Loneliness Scale [28]	3-month	Survey
Secondary	Health-related quality of life	CDC’s Health-Related Quality of Life 4-question core modules, called the “Healthy Days Measures” [29]	3-month	Survey
Exploratory	Nutritional risk	Dietary Screening Tool [30]	3-month	Survey
Exploratory	Emergency department visits	Number of emergency department visits	6-month	Medicare claims
Exploratory	Hospitalizations	Number of acute care hospital admissions	6-month	Medicare claims
Exploratory	Potentially preventable hospitalizations	Number of AHRQ Adult Ambulatory Care Sensitive Condition Admissions [57]	6-month	Medicare claims

The primary study outcome, prioritized by a variety of stakeholders and measured via CMS data for all enrolled participants, is the ratio of the number of days that are spent in an institutional setting (i.e., acute care hospital, psychiatric hospital, long-term care hospital, nursing home, skilled nursing facility) to the number of days alive in the six months following the start of meal delivery.

As a secondary outcome, we are also examining this ratio of days in institutional settings for a period of 3 months after the start of meal delivery. Other secondary outcomes include participant-reported food insecurity, loneliness, and health-related quality of life that are collected during the baseline and follow-up surveys. Food insecurity is measured with the Household Food Security Scale Short Form, which includes six questions about being able to afford food in the last 30 days [27]. Loneliness is measured with the UCLA 3-item loneliness scale, including frequency questions about lacking companionship, feeling left out, and feeling isolated [28]. Four questions are included from the CDC’s Health-Related Quality of Life module to assess quality of life [29]. We chose to assess our secondary person-centered outcomes halfway through the follow-up period because (a) we were able to detect an effect in subjective isolation/loneliness at three months in our prior pilot study [23] and (b) we wanted to minimize potential loss to follow-up for the secondary outcomes.

In response to feedback from our advisory panels, we include the number of emergency room visits, all cause hospitalizations, and potentially preventable hospitalizations ascertained from the CMS data as exploratory outcomes. Additionally, we assess nutritional risk using 26-item food frequency questions during the baseline and follow-up surveys using the Dietary Screening Tool (DST) [30] as an exploratory outcome.

Demographic measures that are included in the baseline survey are marital status, race, ethnicity, level of education, military service, receipt of Veterans Health Administration services, and number of other individuals living in the home. Data on gender and age are provided by the participating programs. Meal delivery data are also provided by the participating programs, including referral status (e.g., accepted or declined meals), meal delivery dates, the number of meals provided on each date, reasons for referral declines, and reasons for meal service terminations. Comorbidities are summarized from the CMS administrative data. Additional questions are included in the follow-up survey to assess participants’ ratings of the meal program overall, delivery method, ease of meal preparation, and taste and amount of food provided. Participants are also asked how much of the food they eat, whether they are still receiving meals, and, if not, why they are no longer receiving meals.

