### Statistical methods

#### Primary outcome analysis

Our primary analysis is an intention-to-treat analysis, meaning that we will assess outcomes for all participants assigned to each group regardless of how long they continue to receive meals. In randomized experiments, the distribution of all the covariates should be similar on average. However, because there are many covariates (e.g., age, education), one may expect that some will suffer from slight imbalances. Using the baseline survey data and participants’ prior Medicare claims, we will test for balance in these covariates between the two arms by comparing means and proportions. To address any minor imbalances and to obtain a more efficient estimate, we will use regression adjustments to estimate the marginal average treatment effect. Because outcomes of individuals within the same household may be correlated, we will use a hierarchical model to adjust for these correlations. Standard errors will be obtained using the bootstrap procedure.

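### The primary and 3-month claims windows start at first meal, after randomisation, which leaves randomised participants who never start without a defined outcome and conflicts with the stated intention-to-treat analysis

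*Protocol article*

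**What the plan says.** The protocol article describes the start of the follow-up window in several places.

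- **Outcomes and measures, text:** the primary ratio has as its denominator "the number of days alive in the six months following the start of meal delivery".
- **Outcomes and measures, Table 1:** "the number of days alive in the 6 months following receipt of meals".
- **Outcomes and measures, 3-month claims outcome:** the same ratio "for a period of 3 months after the start of meal delivery".
- **Introduction:** "a primary endpoint of institutional healthcare use in the 6 months after enrollment".
- **Abstract, Methods:** CMS data are used "to calculate post-randomization institutional vs. community days". No day zero is given.

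The analysis population is everyone randomised. Under Primary outcome analysis, "we will assess outcomes for all participants assigned to each group regardless of how long they continue to receive meals". The outcomes text also says that the primary outcome is obtained from CMS data for all who enrol.

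Randomisation takes place at the end of the baseline survey, before any meal (Recruitment and randomization). Programs supply "referral status (e.g., accepted or declined meals), meal delivery dates" and the reasons for declined referrals (Outcomes and measures). The section on modes of meal delivery says that participants who stop meals stay in the study and are tracked. It gives no rule for those who never start.

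**The concern.** An intention-to-treat analysis needs an outcome window that every randomised person has and that assignment cannot influence. Start of meals meets neither condition.

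A participant who declines the referral, dies or enters an institution before the first meal may have no start date, and then the ratio is undefined. Someone admitted shortly after randomisation whose meals begin after discharge does have a window, but that admission falls outside it.

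The first meal also comes by a different route in each arm: a local program's employee or volunteer in one, a vendor's mailing in the other. Participants know their assignment and have already stated a preference, so acceptance of the first delivery could depend on the arm. People who fail to start are unlikely to have average institutional use. If they fall out of the analysis in unequal numbers, the arm that loses more high-use people looks better with no treatment effect at all. The primary outcome and the 3-month claims outcome are both exposed.

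**Working it through.** **1. Time zero, side by side.** Consent leads straight into the baseline survey, and randomisation closes that survey, so enrolment and randomisation are close to one event. The article therefore has two origins: enrolment or randomisation (Introduction) and first meal (Table 1 and the outcomes text). They coincide only if meals begin at once for everyone.

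**2. Who has a window.** The tracking rule covers people who discontinue, and the intention-to-treat sentence covers any duration of meals. Both presuppose that meals began. For a person who never starts, a count of days from first meal has no day 1.

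**3. The plan's own sample size.** Inputs from Sample size: SDs 0.12 and 0.19, difference 0.02, two-sided α = 0.05, 80% power.
- Common SD = √((0.12² + 0.19²)/2) = √0.02525 = 0.1589.
- n per arm = 2 × (1.960 + 0.842)² × 0.02525 / 0.02² ≈ 991 by the normal approximation. The t-test gives 991.88, so 992 per arm and 1984 in total. The stated figure reproduces.
- Linkage allowance: 2300 × 0.87 = 2001, which is 17 above 1984. No allowance for non-start is stated.

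**4. Possible bias if only starters can be analysed.** The article gives no non-start rate, so these rates are assumptions. Let both arms truly average 0.04, let a fraction p never start, and let non-starters average m. Then the starters' mean = (0.04 − p·m)/(1 − p). The value m = 0.07 is the article's figure for similar people not receiving meals; 0.10 and 0.15 are assumed.

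| m | p = 5% | p = 10% | p = 15% | False difference, 5% vs 10% | False difference, 5% vs 15% |
|---|---|---|---|---|---|
| 0.07 | 0.0384 | 0.0367 | 0.0347 | 0.0018 | 0.0037 |
| 0.10 | 0.0368 | 0.0333 | 0.0294 | 0.0035 | 0.0074 |
| 0.15 | 0.0342 | 0.0278 | 0.0206 | 0.0064 | 0.0136 |

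Against the planned 0.02, the range is 0.0018/0.02 = 9% to 0.0136/0.02 = 68%. If p and m are the same in both arms, the false difference is zero.

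An alternative set-up fixes the lower-risk participants at 0.04 and adds a higher-risk stratum with mean m. Its size is the larger non-start rate, and all non-starters come from it. At 5% vs 15% and m = 0.15:
- overall mean = 0.15 × 0.15 + 0.85 × 0.04 = 0.0565
- starters in the 5% arm = (0.0565 − 0.05 × 0.15)/0.95 = 0.0516
- starters in the other arm = 0.04, so the difference is 0.0116

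At m = 0.07 the difference is 0.0032. The order of magnitude is the same.

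**5. Power, dropping or keeping non-starters.** Power = Φ(δ/(0.1589 × √(2/n)) − 1.96), with equal non-start in both arms. If non-starters are dropped, n shrinks. If they are kept and assumed to show no arm difference, δ becomes 0.02 × (1 − p).

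| Linked total | Non-start (assumed) | Dropped | Kept |
|---|---|---|---|
| 2001 (87% linkage) | 0% | 0.80 | 0.80 |
| 2001 | 5% | 0.78 | 0.76 |
| 2001 | 10% | 0.76 | 0.72 |
| 2300 (full linkage) | 5% | 0.84 | 0.82 |
| 2300 | 10% | 0.82 | 0.78 |

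Keeping non-starters costs more power than dropping them, so the case for a randomisation origin rests on validity and not on power.

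**The case against.** The strongest defence is that nothing in the article says non-starters will be left out. It promises the outcome for all enrolled and all assigned, and it treats the effect of receiving meals as a separate compliance analysis. What is absent is an index date for people without a first meal, and an analysis plan could supply one. This stands in part. A reader might infer that non-starters will be excluded, or that the intention-to-treat analysis cannot be done; the text supports neither. But the article does not leave the origin open. It fixes first meal in the outcome definition and in Table 1, and a plan that followed that wording would inherit the gap.

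A reader might also count the abstract as a third, conflicting origin. It is not one: days after the first meal are also days after randomisation, and the abstract sets no day zero. The real conflict is between the Introduction and the outcomes section.

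It is also tempting to say that the arms get different windows. Both get six months from first meal. A difference in lag is possible because the delivery processes differ, but no lag is reported for either arm.

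On size, the objection is largely right. The rates and their imbalance are assumed, and the article's only no-meals mean, 0.07, gives the low end of the range. The 87% linkage rate comes from probabilistic matching, which the article describes as a fallback for rare cases, so adding non-start to it is pessimistic. With full linkage, losing 5 to 10% leaves 2185 to 2070, still above 1984.

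**Conclusion.** The point holds as a conflict between stated rules. The outcomes section starts both claims windows at an event after randomisation that may not happen. The Introduction starts the primary one at enrolment, and the analysis is promised for everyone assigned. As written, randomised participants who never start have no defined ratio, and institutional days before the first meal are not counted.

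The size of any bias cannot be known from the article. Under the assumed non-start of 5% vs 10 to 15%, with a non-starter mean of 0.07 to 0.15, a starters-only comparison would be off by about 0.002 to 0.014. Equal rate and risk would give zero. These figures show what the wording could allow. They are not an estimate of what will happen. Because the definition concerns the primary outcome, it should be settled before the claims are analysed by arm.

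**What to change.** Define the primary 6-month and secondary 3-month claims windows from the randomisation date, for every randomised and linked participant, whether or not meals start. Keep the window from first meal as a labelled sensitivity analysis. Reconcile Table 1 and the outcomes text with the Introduction, and carry the same wording into the analysis plan and the registry entry. Report non-start and time from randomisation to first meal by arm, using the referral status and delivery dates that programs already supply.

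The change is one of wording. The research team assigns participants and so has the randomisation dates, and the claims are already a planned data source. The cost is dilution: non-starters and days before the first meal enter the comparison. With 87% linkage, and if non-starters show no arm difference, power is about 0.76 at 5% non-start and 0.72 at 10%, against 0.80 with none. With full linkage it is about 0.82 and 0.78. That is the price of the intention-to-treat analysis the protocol has already chosen. If observed non-start is appreciable, the target of 2300 should be reviewed.
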